### Trial design {8}

This is a protocol for a three-arm, randomized, placebo-controlled trial (Fig. 1). It will follow the recommendations and suggestions of the Consolidated Standards of Reporting Trials (CONSORT 2010). The study will be conducted at a 4-week follow-up. Eligible participants will be randomized in a 1:1:1 ratio for enrollment in one of the three groups to receive a high dose of betamethasone MCPI (group H), normal dose of betamethasone MCPI (group N), and non-betamethasone MCPI (group C).

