### Outcomes {12}

#### Primary outcome measures

The primary outcome will be knee pain during 90° flexion via VAS pain score measured by a 10-cm horizontal line scale [19]. The patients will be asked, “How much pain do you have this moment?”, the patient will then mark on the 10-cm horizontal line VAS. Zero means “absence of pain,” while 10 represents “the worst pain” VAS has been proven to be a valid and reliable outcome measure for recording pain with ICC = 0.96 to 0.98, according to a previous study [20]. The VAS score will be evaluated at preoperative day 1; postoperative 6, 24, 48, and 72 h; day 5; day 14; and day 30 following the surgery.

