#### Sample size {14}

The calculation of the sample size was based on previous studies. Ikeuchi et al. [13] reported that the POD 3 VAS scores were 27 ± 16 mm in the steroid group and 43 ± 18 mm in the control group. Kwon et al. [4] reported that POD 3 VAS scores were 35 mm in the steroid group and 41 mm in the control group. We assumed that the mean difference in the VAS score between the high-dose betamethasone group and control group was 0.8, and the mean difference between the normal-dose betamethasone group and control group was 0.4. An estimated standard deviation (SD) of 1.5, significance level (*α*) of 0.05, and power of test (*β*) of 0.8000 will be adopted. Based on the former data, the sample size was calculated as 69 participants per group. Assuming a dropout rate of 10%, the final sample size will be 78 participants per group, and 234 participants will be required for the three groups.

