### Statistical methods

#### Statistical methods for primary and secondary outcomes {20a}

Perioperative outcomes will be summarized using the mean ± SD for continuous variables and the ratio for categorical variables. All statistical analyses will be conducted using the SPSS software (version 13.0. for Windows; SPSS, Inc., Chicago, USA). For continuous variables, the Kolmogorov–Smirnov test will be used to detect the normality of distribution. Analysis of variance (ANOVA) will be used to compare the differences among the three groups, and Dunnett’s *t* test will be conducted to compare the between-group differences. For categorical variables, the chi-square test will be conducted to compare the intragroup differences, and partitions of chi-square methods will be used to compare the between-group differences.

For repeatedly measured outcomes, multivariate analysis for repeated measures ANOVA test will be performed to compare the difference between the three groups, which contains the three intervention groups, time, and group-time interaction. Dunnett’s test will be applied for post hoc comparisons. When the group-time interaction showed a significant difference, a one-way repeated measures ANOVA was conducted to identify the difference in effect between the three intervention groups. The significance level will be set at *α*=0.05. Statistical analyses will be performed by an independent investigator.

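### The follow-up test named after a significant group-by-time interaction, a one-way repeated-measures ANOVA, cannot compare the three independent arms; the error is confined to that step

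*Protocol article*

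**What the plan says.** The protocol article, under Statistical methods for primary and secondary outcomes {20a}, gives two routes for continuous data.

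- In general: "Analysis of variance (ANOVA) will be used to compare the differences among the three groups", with Dunnett's t test for between-group differences.
- For repeatedly measured outcomes: a repeated-measures model "which contains the three intervention groups, time, and group-time interaction", and "Dunnett’s test will be applied for post hoc comparisons". If the interaction is significant, "a one-way repeated measures ANOVA was conducted to identify the difference in effect between the three intervention groups".

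The primary outcome falls under the second route: "The VAS score will be evaluated at preoperative day 1; postoperative 6, 24, 48, and 72 h; day 5; day 14; and day 30". That is one preoperative and seven postoperative measurements, and the outcome section does not single out one of them as primary.

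The design is parallel-group. Under Trial design {8}: "Eligible participants will be randomized in a 1:1:1 ratio for enrollment in one of the three groups".

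**The concern.** The sentence pairs a test with a purpose, and the two do not match. The purpose is to find differences between the three arms. The test has one factor, measured repeatedly on the same patients. In this trial the only factor that repeats within a patient is time.

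At stake is the question that a significant interaction raises: at which times do the arms differ, and does the high or the normal dose differ from control at those times? The group main effect averages over time, and so does a Dunnett comparison built on it, so neither answers that question. The follow-up step is where the plan should answer it. An analyst who runs the named test literally obtains tests of change over time.

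**Working it through.** **1. Can the named test be made to compare arms?** There are three ways to run a one-way repeated-measures ANOVA on these data.

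- *Time as the factor, all patients pooled.* Arm membership does not enter the model.
- *Time as the factor, separately in each arm.* Each F uses one arm's data only, so no F compares arms.
- *Group as the repeated factor.* This needs the same patient, or a matched set, to be observed under all three treatments. The 1:1:1 parallel allocation provides no such sets.

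**2. Invariance to arm differences.** For n patients and T times, with Y(i,t) the score of patient i at time t:

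F = [ n Σ_t (Ȳ(·t) − Ȳ(··))² / (T−1) ] ÷ [ Σ_i Σ_t (Y(i,t) − Ȳ(i·) − Ȳ(·t) + Ȳ(··))² / ((n−1)(T−1)) ]

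Add a constant c(i) to every score of patient i, the same within an arm, and let c̄ be its mean over patients.

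- Numerator term: (Ȳ(·t) + c̄) − (Ȳ(··) + c̄), so the shift cancels.
- Denominator term: the added part is c(i) − c(i) − c̄ + c̄ = 0, so the shift cancels.

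F is therefore the same whatever the constant difference between arms. This is algebra and needs no assumption about correlation or time course.

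**3. Numerical check.** Inputs from Sample size {14}: "the mean difference in the VAS score between the high-dose betamethasone group and control group was 0.8"; "the mean difference between the normal-dose betamethasone group and control group was 0.4"; SD 1.5; 69 per arm. Assumptions not in the document: within-patient correlation 0.5 and a falling VAS course over the seven postoperative times (5, 4.5, 4, 3.6, 3.2, 2.5, 2.0 cm). One data set was generated and the arms were then shifted by 0, −0.4 and −0.8.

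| One-way repeated-measures F | Before shift | After shift |
|---|---|---|
| Pooled | 213.02 | 213.02 |
| Arm 1 | 72.84 | 72.84 |
| Arm 2 | 64.51 | 64.51 |
| Arm 3 | 76.18 | 76.18 |

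In 2,000 simulated trials with flat time courses and arms differing by 0/0.4/0.8, the pooled repeated-measures test rejected in 4.85%, which is its nominal level. A between-group one-way ANOVA at 72 h rejected in 80.2%. With identical arms, the between-group ANOVA at 72 h rejected in 4.4%.

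**4. The plan's own sample size.** A between-group one-way ANOVA with means 0, 0.4 and 0.8 has grand mean 0.4 and squared deviations 0.16 + 0 + 0.16 = 0.32. The noncentrality is λ = n × 0.32 / 1.5² = 69 × 0.32 / 2.25 = 9.81, with 2 and 3 × 68 = 204 degrees of freedom. At α = 0.05 the power is 0.8015; at n = 68 it is 0.7953. The stated 69 per group is reproduced. It rests on a between-group ANOVA, not on the follow-up test in question, so it does not move.

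**5. What the time-averaged effect hides.** As an illustration only, suppose H and C differ by 0.8 at 24, 48 and 72 h and by nothing at the other four postoperative times. The average difference is 3 × 0.8 / 7 = 0.34. A constant difference of 0.34 at all seven times gives the same average. Only comparisons at each time separate the two patterns.

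**The case against.** The strongest reply is that the phrase is a loose label. It may stand for a one-way between-group ANOVA at each time, or for a model with one between-patient factor and repeated measures. The stated purpose is to compare the three groups, and the sentence slips into the past tense in a plan otherwise written in the future, which suggests hasty drafting. That may well be so. But the text does not say it, and the same section uses plain ANOVA where it means a comparison of groups. A plan that needs this guess should be reworded.

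The second reply is that valid between-arm tests remain: the group and interaction terms, Dunnett's test, and ordinary ANOVA with Dunnett's t test. This stands, and it limits the point. None of them is expressly tied to each time point after an interaction, so the gap is in the follow-up only.

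Some stronger readings are tempting, and the document does not support them.

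- *The primary outcome would be decided by within-arm tests, with significance in H but not in C read as an effect.* The protocol never directs that reading.
- *There would be no estimate of dose versus control.* Dunnett comparisons are planned.
- *This step is likely to decide the trial.* An interaction is plausible: the Discussion cites a meta-analysis with benefit on postoperative days 1 to 3 and no significant difference later. But that was pain at rest, while this trial measures pain in flexion, and the Discussion also cites trials with no pain benefit.
- *How often the test rejects when pain falls measures a false-claim rate.* It would reflect only the assumed fall, and would ignore that the step is run only after a significant interaction.

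One limit of the working also stands. The invariance is for constant shifts. If arms differ in time profile, each within-arm F depends on that arm's own profile. It is still not a comparison with another arm.

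**Conclusion.** The point holds as an error in a stated rule, not as missing detail. Taken literally, the named follow-up cannot compare three independent arms. This follows from the parallel design and from the algebra; the simulated percentages depend on the assumed correlation and time course, but the conclusion does not.

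Its reach is one step. The main model, Dunnett's test and the 69 per group are untouched. It deserves correction before analysis because the step applies to the primary VAS outcome, which has seven postoperative times and no named primary time, and because a follow-up chosen after the data are seen would leave the choice of time-specific comparisons open to selection.

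**What to change.** Replace the sentence with: *If the group-time interaction is significant, the three groups will be compared at each time point by between-group simple effects (contrasts from the same model, or a one-way between-group ANOVA), with Dunnett comparisons of H and N against C and adjustment for the number of time points.*

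This changes one sentence and needs no new data and no change in sample size. Confidence intervals or baseline adjustment would be useful but are not needed to cure the error.

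The price is that each time-specific comparison becomes more conservative. At an unadjusted 0.05, the three-group ANOVA at one time has power 0.80 with 69 per group (step 4). Plain Bonferroni over seven times tests at 0.05 / 7 = 0.0071; with the same λ = 9.81 and 2 and 204 degrees of freedom, power is 0.55. A stepwise method such as Holm, or one that uses the correlation between times, loses less. The adjustment method should be named in advance.

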#### Interim analyses {21b}

No formal interim efficacy analyses will be conducted. Recruitment and withdrawal rates will be reviewed during the trial on an ongoing basis. The trial steering committee will review the information on the progress and accruing data of the trial (e.g., recruitment rates, data quality, adherence to protocol treatment and follow-up, main study outcomes, and safety data) and will possess the ability to propose protocol changes, modify target recruitment, and in exceptional circumstances prematurely terminate the trial.

#### Methods for additional analyses (e.g., subgroup analyses) {20b}

Not applicable. No subgroup will be established in this study.

#### Methods in analysis to handle protocol non-adherence and any statistical methods to handle missing data {20c}

An intention-to-treat analysis will be conducted according to the allocation of the original group. If any participant withdraws from the trial, the last observation carried forward method and multiple imputation method will be implemented for missing data adjustment.

#### Plans to give access to the full protocol, participant level-data and statistical code {31c}

The datasets analyzed during the current study will be available from the corresponding author upon reasonable request.

### Oversight and monitoring

#### Composition of the coordinating center and trial steering committee {5d}

The trial steering committee will be formed by the chief investigator, one investigator in this study, the coordinating center, and the administrative staff of the orthopedics department. It will be an independent group responsible for oversight of the trial and ensuring that the trial is performed according to Good Clinical Practice in order to safeguard the participants.

The coordinating center will be composed of two main investigators in this study: staff in the operating room and orthopedics clinic. They will assist with the coordination and strategic management of the trial.

#### Composition of the data monitoring committee, its role, and reporting structure {21a}

The data monitoring committee will consist of two main investigators (responsible for data administration) and staff in the ethics committee. It will be independent of the sponsor and competing interests and will be responsible for safeguarding the interests of the participants and monitoring the accumulating data.

#### Adverse event reporting and harms {22}

All SAEs will be recorded in the medical records and case report forms, including the onset date, complete description of the event, severity, duration, action taken, and outcome. The chief investigator will complete the SAE form, and the form will be emailed to the ethics committee of The Second Affiliated Hospital within five working days of awareness of the event. The chief investigator will respond to any SAE queries raised by the ethics committee as soon as possible. All common adverse events will be recorded on the case report forms.

#### Frequency and plans for auditing trial conduct {23}

The data monitoring committee will report the study progress in the form of weekly research meetings. Meanwhile, the Trial Steering Group and Ethics Committee will meet monthly to review conduct throughout the trial period.

#### Plans for communicating important protocol amendments to relevant parties (e.g., trial participants, ethical committees) {25}

Any important protocol modifications, including the principal investigator, informed consent form, study protocol regarding eligibility criteria, outcomes, and analyses, will be reported to all investigators, Trial Steering Committee, trial participants, trial registry, and ethics committee of the Second Affiliated Hospital, Guangzhou University of Chinese Medicine.

#### Dissemination plans {31a}

The results will be reported in conferences or peer-reviewed journals. There are no terms or conditions for funding that could affect publication and dissemination.

## Discussion

In TKA, an enhanced recovery strategy warrants improved patient comfort during hospital stay and accelerated discharge. Consequently, measures to control pain and accelerate rehabilitation are important. Although the MCPI technique has been proven to be a safe and cost-effective measure, the gold standard for drug combinations has not yet been established. Corticosteroid addition to MCPI is believed to be a key component owing to its local anti-inflammatory effects and ability to reduce the local stress response following surgery. However, there is conflicting evidence regarding its benefits for pain control following TKA. Christensen et al. [18] conducted a randomized controlled trial that compared patients who had MCPI with 40 mg of methylprednisolone or without corticosteroids, and the only significant result was a decreased LOS in the steroid cohort (2.6 vs. 3.5 days). There was no difference in pain scores, ROM, or Knee Society scores at any time point. Chia et al. [17] compared patients who had an MCPI containing high- or low-dose corticosteroid with patients’ MCPI without corticosteroid, and they were unable to find any significant clinical effect on postoperative ROM advantage and pain relief at the two different dosages. In contrast, Seah et al. [16], who used 40 mg of triamcinolone acetate, found a significant reduction in the early postoperative pain scores and lasting increase in the ROM in the steroid group. Wang et al. [10] found that addition of corticosteroids to an analgesic cocktail could prolong the analgesic effects of local anesthetics, reduce inflammation, slightly improve immediate postoperative pain relief, and accelerate recovery in the first 24 h following TKA. They concluded that the additional analgesic effects of corticosteroids were mild and transient, and prospective studies are still needed to determine the best cocktail of periarticular infiltration analgesia. A meta-analysis by Chai et al. [29] demonstrated that cocktail analgesia containing corticosteroid periarticular injection did not contribute to pain relief within 12 h postoperatively; however, from 24 to 72 h, it significantly decreased the pain score at rest and reduced total rescue opioids. A recent meta-analysis by Li et al. [30] demonstrated that adding corticosteroids to multimodal cocktail periarticular injection can relieve the POD 1, POD 2, and POD 3 pain intensity at rest following TKA, with no significant difference in the VAS score at the operation night, POD 4, POD 5, POD 7, and 2 weeks following the operation. Owing to these conflicting results, we plan to design a three-arm, double-blinded randomized controlled trial containing a high or normal dose of corticosteroid MCPI and a noncorticosteroid MCPI to assess their effectiveness in postoperative pain relief, functional improvement, rescue analgesia, and side effects. This study will also provide clinical evidence on the effect of high-dose corticosteroid adjuvant to MCPI on prolonged pain control and better recovery following TKA.

## Trial status

Recruitment commenced in October 2020, and the trial is scheduled to end in July 2022.

## Data Availability

The datasets used and/or analyzed during the current study will be available from the corresponding author upon reasonable request.

## Abbreviations

TKA: Total knee arthroplasty
MCPI: Multimodal cocktail periarticular injection
POD: Postoperative day
OA: Knee osteoarthritis
VAS: Visual analog scale
ROM: Range of motion
CRP: C-reactive protein
ESR: Erythrocyte sedimentation rate
IL-6: Interleukin 6
Glu: Blood glucose
SAE: Serious adverse events
